#### Postoperative procedures

Postoperative patients are visited daily by a surgical resident and discussed twice a week by a multidisciplinary team including an orthopaedic trauma surgeon, ward doctor, trauma nurse, physiotherapist, dietician, geriatrician and transfer nurse. In our study hospital, hip fracture patients are preferably discharged 3 days after surgery according to local protocol. Patients are discharged home if pain is manageable, no active complications are present, and if mobility is adequate for living independently (meaning that the patient can safely make indoor transfers) or if home care is available and sufficient. If home care is not sufficient, discharge to one of the nursing homes specializing in hip fracture rehabilitation is planned. These assessments are also made by the multidisciplinary team for all patients twice a week. All patients fit for rehabilitation will be invited for outpatient check-ups 6 weeks, 3 months and 12 months after surgery. The reasons for failure to follow up will be recorded.

The outpatient check-ups include consultations by a trauma surgeon or surgical resident, a physiotherapist for mobility assessments and a geriatrician for strength and balance assessments and osteoporosis screening and treatment. A timeline with the scheduled procedures and assessments is presented in Table 2.

### Sample size

Reported one-year postoperative results for the HHS in hemiarthroplasty patients vary between 68 (standard deviation [SD] 20 [24] and 78 (SD 10) [25]. Long-term (12 months) postoperative HHS results for specific surgical approaches are lacking in literature. For the sample size calculations a difference in functionality of 10 points as measured by the HHS was considered clinically relevant [26], with a standard deviation of 15. To detect this difference two equally sized cohorts of at least 41 patients with a complete 12 months follow-up are necessary (α = 0.05, power = 80%). Anticipating failure to follow up of 40%, inclusion of at least 69 patients per intervention group, or 138 in total, is required.

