## Abstract

**Background:**

The Direct Anterior Approach (DAA) is an alternative approach to the currently most used Lateral Approach (LA) for hip replacement in femoral neck fracture patients. Compared to the LA, the DAA minimizes soft tissue damage. Sparing muscle tissue may facilitate early and improved postoperative mobility. It may also be associated with fewer complications, increased quality of life and lower 1-year mortality. The aim of this study is to compare postoperative complications, hip function and patient mobility after hemiarthroplasty via the anterior or lateral approach following a displaced femoral neck fracture.

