**Methods:**

138 elderly patients with displaced femoral neck fractures will be operated using either the direct anterior approach or the lateral approach for a hemiarthroplasty in a single centre, prospective, comparative cohort study. The choice of surgical approach will depend on the expertise of the trauma surgeon on call. The primary outcome of this study will be the functionality of the hip after surgery measured using the Harris Hip Score during routine outpatient check-ups. Secondary outcomes include surgical and non-surgical complication rates, admission time, postoperative pain, rehabilitation time, performance in activities of daily living, health-related quality of life measured, cognitive function and balance.

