### Statistical analysis

Demographic and clinical characteristics of the cohorts will be described using summary statistics and will be compared by univariate analysis. Categorical variables will be compared using the chi-squared test if the data are sufficiently large (expected cell counts >5) or the Fisher’s exact test if this requirement cannot be met. Continuous variables will be compared by unpaired t-tests for normally distributed data, and by the Wilcoxon rank sum test for not normally distributed data.

Outcome parameters will be compared univariably between cohorts, but correction for confounding factors is of major importance because the patients in this study are not randomized. Since the number of study participants is limited relative to the number of potential confounders, a propensity score will be calculated from the available baseline parameters. The propensity score will be used to adjust for differences between the two cohorts in multivariable linear regression analyses for continuous outcome parameters and in multivariable logistic regression analyses for binary outcomes. Repeated outcome measures such as the HHS and pain score will also be analysed using Generalized Linear Models. *P*-values <0.05 will be considered statistically significant. All statistical analyses will be performed using IBM SPSS Statistics version 20.0 or higher.

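### The stated inputs give 37 completers per group, not 41 (41 gives about 85% power, a conservative mismatch), and 138 in total equals 69 per group only at a 1:1 split

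*Protocol article*

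**What the plan says.** The Sample size section of the protocol article sets the target from four inputs. The difference: "a difference in functionality of 10 points as measured by the HHS was considered clinically relevant". The spread: "with a standard deviation of 15". The error rates: "α = 0.05, power = 80"%. From these it concludes that "two equally sized cohorts of at least 41 patients with a complete 12 months follow-up are necessary". It then allows for 40% failure to follow up and states that "inclusion of at least 69 patients per intervention group, or 138 in total, is required". The section names no test, sidedness or further allowance.

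On how patients reach a cohort, the abstract says: "The choice of surgical approach will depend on the expertise of the trauma surgeon on call". The Surgical procedures section says the same, and Study population describes consecutive inclusion. Statistical analysis notes that patients are not randomised, names a t-test or Wilcoxon rank sum test for unadjusted comparisons of continuous variables, and plans propensity-score-adjusted regression. Its significance rule, for P, is "values <0.05 will be considered statistically significant". The abstract gives the study size simply as 138.

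**The concern.** There are two separate problems.

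First, the section prints both its inputs and its result, and the two do not agree. A reader who repeats the calculation cannot tell whether the power, the SD or the assumed test is misreported, and this is the figure on which the study size rests.

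Second, a minimum of 69 in each group and a total of 138 are presented as one requirement. They coincide only when the cohorts are exactly equal. Here the approach is set by which surgeon is on call, and no balancing step is described. If recruitment closes on the total, the smaller cohort may fall short of its minimum, and the stated power would then not describe the study that was done.

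**Working it through.** **Inputs.** From Sample size: difference 10, SD 15 (standardised difference 10/15 = 0.667), alpha 0.05, power 80%, equal groups, 40% loss. Sidedness is not stated. I assume two-sided and also show one-sided.

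**Step 1: the plan's own chain from 41 onward.** 41/(1 − 0.40) = 68.3, rounded up to 69, and 2 × 69 = 138. The loss step is correct.

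**Step 2: completers per group from the stated inputs.**
- Normal approximation: n = 2 × (1.960 + 0.842)² × (15/10)² = 35.3, so 36.
- Noncentral t: 36.3, so 37. Power is 79.7% at 36 and 80.8% at 37.
- Enrolled after 40% loss: 37/0.6 = 61.7, so 62 per group and 124 in total.

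The stated 41 is not reproduced. The gap is 4 completers per group, or 7 enrolled per group (69 − 62) and 14 in total (138 − 124).

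**Step 3: power at 41 per group.** 84.7% by noncentral t, 85.5% by normal approximation.

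**Step 4: what would produce 41?**
- One-sided test, 80% power: 28 (normal) or 29 (t). This does not explain it.
- Two-sided, 85% power: 2 × (1.960 + 1.036)² × 2.25 = 40.4, so 41 (normal); 42 by t.
- SD 16, 80% power: 2 × (1.960 + 0.842)² × (16/10)² = 40.2, so 41 (normal); 42 by t.
- Rank-test allowance at the worst-case efficiency of 0.864: 35.3/0.864 = 40.9, so 41 (normal); 43 by t. At the efficiency for normal data, 0.955, it is 39 by t.

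Three routes reach 41, and the section states none of them.

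**Step 5: cohort split with 138 enrolled.** The documents do not give the split between approaches, so the splits below are assumptions. Completers are taken as 0.6 × enrolled in each cohort, unrounded, with SD 15 and a two-sided t-test.

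| Enrolled | Completers | Power |
|---|---|---|
| 69:69 | 41.4 : 41.4 | 85% |
| 92:46 | 55.2 : 27.6 | 81% |
| 100:38 | 60.0 : 22.8 | 76% |
| 110:28 | 66.0 : 16.8 | 67% |

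Power passes below 80% just beyond 2:1 (93:45 gives 80.2%, 94:44 gives 79.8%). The per-group minimum fails sooner, at any split other than 69:69. For the smaller cohort to reach 69, the total would have to be 69/0.4 = 172.5, so 173, at 60:40, and 69/0.3 = 230 at 70:30.

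**The case against.** The best defence has three parts, and much of it stands.

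*The mismatch is harmless.* The section asks for at least 41, which is more than a t-test needs. On the stated inputs no cohort is too small. This is right, and it is why the enrolment target need not change.

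*41 may be an unreported allowance rather than a slip.* The Wilcoxon test is named in Statistical analysis, and a worst-case rank-test allowance reaches 41. A condensed article may leave such detail to the full protocol. This is fair as to cause. The article nevertheless prints a complete set of inputs with a result that does not follow from them, so the paragraph as written is wrong whichever explanation applies.

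*A per-group minimum is already stated.* This is true, and stopping at 138 with 100:38 would breach it. What remains is that the same sentence offers the total as equivalent, and the abstract carries only the total.

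A reader might also infer more than the documents support:
- *That the lateral approach will dominate here.* The abstract calls the anterior approach "an alternative approach to the currently most used Lateral Approach (LA"), but that describes general practice. Surgical procedures says both approaches are standard in this hospital, and no local split is given.
- *That propensity adjustment or surgeon clustering brings power below 80%.* The documents give no figure for how well baseline variables predict the approach, nor for correlation within surgeon. Adjustment may also remove outcome variance, which works the other way.
- *That an imbalance would go unseen.* Surgical approach is among the recorded baseline parameters, so cohort sizes can be followed throughout.

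**Conclusion.** The point holds as a reporting error in the conservative direction, together with loose wording of the target. On 10 points, SD 15, two-sided 0.05 and 80% power, the requirement is 37 completers per group (62 enrolled per group, 124 in total). The planned 41 give about 85% for an unadjusted, equal-sized, independent comparison. This rests on alpha being two-sided; a one-sided reading moves the figure further from 41.

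The total of 138 delivers 69 per group only at 1:1, which the design does not secure. Power remains above 80% to about 2:1, so the documents do not show that the study is underpowered. They show that the stated power does not belong to the stated inputs, and that it will need restating once the split is known.

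**What to change.** 1. Keep the enrolment target and correct the statement, for example: for a 10-point difference, SD 15 and a two-sided alpha of 0.05, 37 completers per group give 80% power; the planned 41 give about 85% for an unadjusted t-test with equal groups. If 41 came from a rank-test allowance, another SD or a different power, name that instead.
2. Make the per-group minimum of 69 the target, drop 138 in total as its equivalent (including in the abstract), and commit to restating power for the split reached. A short table of power by split, marked as assumed, would serve.
3. Label the calculation as unadjusted, since the planned analysis adjusts by propensity score. Any loss from adjustment or surgeon clustering should appear only as an assumed scenario.

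The cost is one reworded paragraph, a matching phrase in the abstract and an optional small table. Holding to the per-group minimum may lengthen recruitment if the split is uneven: at 60:40 the total would be 173 rather than 138.

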### Statistical analysis

Demographic and clinical characteristics of the cohorts will be described using summary statistics and will be compared by univariate analysis. Categorical variables will be compared using the chi-squared test if the data are sufficiently large (expected cell counts >5) or the Fisher’s exact test if this requirement cannot be met. Continuous variables will be compared by unpaired t-tests for normally distributed data, and by the Wilcoxon rank sum test for not normally distributed data.

Outcome parameters will be compared univariably between cohorts, but correction for confounding factors is of major importance because the patients in this study are not randomized. Since the number of study participants is limited relative to the number of potential confounders, a propensity score will be calculated from the available baseline parameters. The propensity score will be used to adjust for differences between the two cohorts in multivariable linear regression analyses for continuous outcome parameters and in multivariable logistic regression analyses for binary outcomes. Repeated outcome measures such as the HHS and pain score will also be analysed using Generalized Linear Models. *P*-values <0.05 will be considered statistically significant. All statistical analyses will be performed using IBM SPSS Statistics version 20.0 or higher.

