#### Secondary outcomes

##### Clinical outcomes

Surgical parameters: mean operation time (skin-to-skin), mean total blood loss.Surgical complication rates (postoperative bleeding,^1^ haematoma formation, implant failure, implant dislocation,^2^ implant luxation, femoral head necrosis, periprosthetic fractures,^3^ superficial wound infection,^4^ deep wound (prosthesis) infection,^5^ nerve damage^6^).Cognitive status measured with the 6CIT score [12, 13] at admission to the hospital and at 6 weeks, 3 months and 12 months after surgery, and DOS scores during admission [14].Duration of hospital stay, cause of delayed discharge (considered later than 72 h after surgery), discharge destination and duration of rehabilitation (in days).Readmission and operative revision rate.1-year mortality.^7^
Non-surgical complications up to 12 months after surgery (delirium,^8^ anaemia,^9^ cardiac complications (decompensation and ischemia), CVA, pressure sores,^10^ electrolyte disturbances, pulmonary embolism,^11^ pneumonia,^12^ renal failure, sepsis,^13^ deep venous thrombosis^14^ and urinary tract infections^15^).Functionality and balance through a series of physiotherapeutic tests (Short Physical Performance Battery [15], Timed Up and Go test [16], Functional Ambulatory Categories [17]) at 6 weeks, 3 months and 12 months after surgery.Pain measured using a visual analogue scale (VAS) during in-hospital treatment and at 6 weeks, 3 months and 12 months after surgery.Patient-reported performance in activities of daily living using the Katz ADL Index [18] at 6 weeks, 3 months and 12 months after surgery.Health-related quality of life using the EQ-5D questionnaire [19, 20] at 6 weeks, 3 months and 12 months after surgery.

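### Rehabilitation duration falls under adjusted linear regression, which cannot represent death before completion or an unknown end date, so the approach with more early deaths tends to look faster

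*Protocol article*

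**What the plan says.** Protocol article, Statistical analysis: the propensity score is used to adjust "multivariable linear regression analyses for continuous outcome parameters" and to adjust "in multivariable logistic regression analyses for binary outcomes". Generalized Linear Models are added for repeated measures such as the Harris Hip Score and pain. The unadjusted comparison of continuous variables is by t-test or "by the Wilcoxon rank sum test for not normally distributed data". The section names no time-to-event method, and it calls correction for confounding a matter of major importance.

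Protocol article, Clinical outcomes (under Secondary outcomes): the list includes "Duration of hospital stay, cause of delayed discharge (considered later than 72 h after surgery"), "discharge destination and duration of rehabilitation (in days") and, separately, "1-year mortality". The two durations are not named in the analysis section. They fall under linear regression because they are continuous and measured once.

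On incomplete follow-up, Sample size has "Anticipating failure to follow up of 40" per cent, and Postoperative procedures has "The reasons for failure to follow up will be recorded".

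**The concern.** Rehabilitation ends on a date that a patient may not live to reach, or that the study may never learn. The patients are 70 or older and mortality is itself an outcome, so some will die before the end. A linear model on days has no way to say that rehabilitation had not ended when the patient died or was last seen. The analyst must either use the day of death as if it were the end, or drop the patient. The first shortens the mean directly. The second removes long durations preferentially, because a longer rehabilitation leaves more time in which to die or lose contact. The rank test shares the problem and is unadjusted as well.

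The Discussion names faster rehabilitation and shorter admission among the gains that identifying the best approach could bring. If early mortality differs between approaches, this comparison would partly measure survival and report it as speed of recovery.

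**Working it through.** **Inputs.** The article gives no expected rehabilitation time, length of stay or mortality, so there is no figure of its own to reproduce on this point. The group size is taken from Sample size: 41 / (1 − 0.40) = 68.3, hence 69 per group. Everything else is assumed:
- rehabilitation time T follows a gamma distribution with shape 2 and mean μ of 30, 42 or 60 days, identical in both groups;
- a proportion m of patients die, at times D uniform over days 0 to 90, independent of T;
- m is 10% in one group and 20% or 30% in the other.

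**Formulas.** Let e be the mean of min(T, D) among patients who die by day 90, p the proportion of them who finish rehabilitation first, and c the mean duration of those finishers.
- Death entered as the end date: mean = (1 − m)μ + m·e. The false difference between groups is (m_B − m_A)(μ − e).
- Deaths before completion dropped: mean = [(1 − m)μ + m·p·c] / [(1 − m) + m·p].

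**Worked case, μ = 42.** Numerical integration gives e = 27.79, p = 0.554, c = 27.82.
- End-date coding: 0.9 × 42 + 0.1 × 27.79 = 40.58, against 0.8 × 42 + 0.2 × 27.79 = 39.16. The false advantage is 1.42 days.
- Dropping: (37.8 + 1.541) / 0.9554 = 41.18, against (33.6 + 3.083) / 0.9108 = 40.28. The false advantage is 0.90 day.

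**All cases.** Days by which the higher-mortality group looks faster, and the false-positive rate at nominal 5% (3,000 simulated unadjusted comparisons, 69 per group):

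| Mean (days) | Early mortality | Death as end date | Deaths dropped | False positives (end date / dropped) |
|---|---|---|---|---|
| 30 | 10% v 20% | 0.7 | 0.5 | 5.1% / 4.8% |
| 30 | 10% v 30% | 1.5 | 1.1 | 7.8% / 6.5% |
| 42 | 10% v 20% | 1.4 | 0.9 | 5.7% / 5.1% |
| 42 | 10% v 30% | 2.8 | 1.9 | 7.9% / 5.7% |
| 60 | 10% v 20% | 2.7 | 1.4 | 6.6% / 5.5% |
| 60 | 10% v 30% | 5.4 | 3.0 | 10.9% / 6.4% |

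The simulated differences agree with these exact ones to about 0.15 day. With equal mortality in both groups the false difference is zero.

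**A second distribution.** With log-normal T (median 42 days, log-SD 0.6) and exponential death times, 90-day mortality of 10%, 20% and 25% gives means of 48.2, 46.1 and 45.1 days with death as the end date. That is a false advantage of 2.1 and 3.2 days. Dropping deaths gives 49.1, 47.8 and 47.1 days, or 1.3 and 1.9 days. The direction is the same.

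**Unknown end dates, equal in both groups.** Under the same log-normal model with a true 25% longer duration in one group, the real difference is 12.6 days. Dropping patients lost before completion, with 10%, 20% or 30% lost by day 90 in each group, shrinks it to 11.9, 11.2 and 10.6 days.

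**Hospital stay.** With an assumed gamma mean of 6 days and in-hospital death from 2% v 6% up to 2% v 10%, the simulated shift is 0.14 to 0.27 day with death as the end date and 0.05 to 0.08 day with deaths dropped.

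**The case against.** The strongest reply has four parts.

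1. How deaths and unknown end dates enter a secondary duration is detail that a condensed article commonly leaves to a statistical analysis plan, and none is shown. This stands as far as the missing rule goes. It does not cover the choice of model: linear regression is stated, and no rule for entering deaths lets it represent an unfinished rehabilitation.

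2. A reader might infer that the plan counts death as a short stay or a quick recovery. The article does not say so. Dropping those patients is equally open and gives a smaller bias, roughly half to three quarters as large in the table above.

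3. A reader might also infer that 40% of rehabilitation end dates will be unknown. That figure concerns complete 12-month follow-up for the Harris Hip Score. Its split between death and other loss is not given, and rehabilitation may well end before most of that loss occurs. Loss to follow-up hardly touches hospital stay, which is observed on the ward. Ability to rehabilitate is judged during admission (Study population), so some early in-hospital deaths may never enter the cohort.

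4. The size is modest. For a gamma with shape 2 the SD is μ/√2, so the standard error of a difference at 69 per group is μ/√69, or 5.1 days at μ = 42. A 1.4-day shift is under 0.3 of that. The mortality contrasts assume at least a doubling between approaches, and 1-year mortality will be reported beside the durations. All of this stands and limits the weight of the point.

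Nor do the documents show that the bias would flatter the anterior approach. The Abstract suggests lower 1-year mortality with it. If early mortality were lower too, the bias would run against it.

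**Conclusion.** The point holds in a limited form. The stated model does not suit rehabilitation duration. Both ways of forcing deaths into it favour the approach with more early deaths, and dropping unknown end dates can also understate a real difference. On the assumptions shown, the false advantage is about 0.5 to 5 days and the false-positive rate about 5% to 11%, with the upper ends needing a threefold mortality difference and a long mean rehabilitation. The simulations used unadjusted comparisons. Propensity adjustment balances baseline differences but does not restore an end date that death prevented. The effect on hospital stay is a fraction of a day. This concerns secondary outcomes only and leaves the Harris Hip Score conclusion untouched, so it is a cheap improvement and not a threat to the study.

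**What to change.** In Statistical analysis, take duration of rehabilitation, and preferably hospital stay, out of the linear-regression rule. Suggested wording: *Time to end of rehabilitation and time to discharge alive will be compared with propensity-score-adjusted cause-specific Cox models. Death is a competing event, and patients whose end date is unknown are censored at last contact. Cumulative incidence of completion and of death will be shown by approach.*

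In the scenario tested above, the cause-specific hazard of completion is identical in the two groups, so the false advantage disappears. The cumulative incidence shows the deaths openly: at μ = 42, eventual completion is 0.9 + 0.1 × 0.554 = 95.5% at 10% mortality and 0.8 + 0.2 × 0.554 = 91.1% at 20%.

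Cost: a sentence or two of wording and a little programming. The cause-specific Cox model runs in the planned software. It needs the date of death or last contact for patients who do not complete. The results are hazard ratios and cumulative incidences instead of a difference in mean days, which clinicians may find less direct. Censoring at last contact still assumes that loss is unrelated to recovery given the propensity score, so the recorded reasons for loss should be reported by approach.

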### Treatment and procedures

Patients admitted to the hospital with a proximal femoral fracture will be treated according to the treatment guidelines for proximal femoral fracture in the elderly of the Nederlandse Vereniging voor Heelkunde (Dutch trauma surgery society) [23]. A timeline with all scheduled data registrations and assessments is presented in Table 2
*.*

**Table 2 Tab2:** Timeline for scheduled procedures and assessments

Procedure/Assessment	Admission	In-hospital treatment phase	6 weeks after surgery^a^	3 months after surgery^a^	12 months after surgery^a^
*Baseline measurements*	X				
*Physical examination*	X	X	X	X	X
*X-ray assessment*	X				
*Katz ADL*	X		X	X	X
*EQ-5D*	X		X	X	X
*6CIT*	X		X	X	X
*SNAQ*	X				
*VAS pain*		X	X	X	X
*Complication* ^*a*^ *registration*		X	X	X	X
*Mobility tests* ^*b*^			X	X	X

^a^Any patient reported complication in the previously described surgical and non-surgical complication list and any reason for a postoperative readmission to a hospital

^b^HHS, SPPB, TUG, FAC

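### The model named for repeated HHS and pain scores carries no within-patient correlation; fitted as named, it would misstate the error of visit-averaged and approach-by-visit tests

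*Protocol article*

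**What the plan says.** The Statistical analysis section of the protocol article sets out three layers for continuous outcomes: a univariable comparison of the cohorts, a linear regression adjusted for a propensity score, and then, for outcomes measured more than once, this sentence: "Repeated outcome measures such as the HHS and pain score will also be analysed using Generalized Linear Models". No correlation structure, random effect, clustering by patient or robust standard error is mentioned. SPSS is named as the software, but no procedure within it. The section's threshold is general: P-"values <0.05 will be considered statistically significant".

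Table 2 schedules the mobility tests at 6 weeks, 3 months and 12 months, and its footnote lists them as "HHS, SPPB, TUG, FAC". The HHS therefore has three occasions per patient. Pain is scored during the hospital stay and at the same three visits, so at least four times.

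The Sample size section is tied to one time point: "two equally sized cohorts of at least 41 patients with a complete 12 months follow-up are necessary". The Primary outcome section names the HHS without a time point.

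**The concern.** Scores from the same patient at successive visits are usually positively correlated. A model that treats them as separate independent observations counts more information than there is when it averages the approach effect over visits. The standard error is then too small and chance differences are declared significant too often. For comparisons within a patient over time the error runs the other way: the shared patient level cancels, the model does not know this, and the test loses power.

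This matters here for two reasons. The HHS is the primary outcome, and the Statistical analysis section does not rank the repeated-measures analysis against the regression. And the background puts weight on early recovery, which an approach-by-visit test would address.

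**Working it through.** **The plan's own figures.** They concern the 12-month comparison and give the setting.
- Inputs from the Sample size section: "a difference in functionality of 10 points as measured by the HHS was considered clinically relevant"; "with a standard deviation of 15"; "α = 0.05, power = 80"%.
- Normal approximation, two-sided: n = 2 × (15/10)² × (1.96 + 0.84)² = 35.3, so 36 per group. The exact t-test gives 36.3, so 37.
- The stated 41 is larger. It is reached with a rank-test allowance, 35.3/0.864 = 40.9, which the text does not state. At 41 per group the t-test has 84.7% power, so the figure is on the safe side.
- Loss to follow-up: 41/(1 − 0.40) = 68.3, so 69 per group and 138 in total, as stated.

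This calculation uses one value per patient. Correlation between visits does not enter it.

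**Inputs for the repeated-measures check.**
- Number of occasions m: 3 for the HHS; 4 for pain, counting the hospital stay once.
- Nominal level: 0.05, taken as two-sided.
- Within-patient correlation ρ: not given in the documents. It is an assumption, shown over a range, and taken as equal between all visits.
- Every patient is taken to have all visits.

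**Approach effect averaged over visits.** If m correlated values are analysed as independent, the variance is understated by the factor D = 1 + (m − 1)ρ. The true error of a 5% test is 2 × [1 − Φ(1.96/√D)].

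| ρ (assumed) | D, m = 3 | True error, m = 3 | D, m = 4 | True error, m = 4 |
|---|---|---|---|---|
| 0.3 | 1.6 | 12.1% | 1.9 | 15.5% |
| 0.5 | 2.0 | 16.6% | 2.5 | 21.5% |
| 0.7 | 2.4 | 20.6% | 3.1 | 26.6% |
| 0.8 | 2.6 | 22.4% | 3.4 | 28.8% |

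For three visits, the full span for ρ from 0.1 to 0.9 is 7.4% to 24.2%. The error reaches 15% at ρ = 0.43 and 20% at ρ = 0.67.

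**Simulation.** 20,000 data sets with 41 patients per group, three visits and SD 15 gave the following true errors.
- Equal correlation, visits analysed as independent: 12.4%, 17.2%, 20.5% and 22.7% at ρ = 0.3, 0.5, 0.7 and 0.8.
- Correlation decaying with distance between visits, analysed as independent: 10.9%, 15.1%, 19.3% and 21.9%.
- Same data analysed through patient means, which respects the correlation: 4.8% to 5.2%.

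**Approach-by-visit contrasts.** Here the true variance is the assumed one multiplied by (1 − ρ), so the true error is 2 × [1 − Φ(1.96/√(1 − ρ))]. This is 1.9% at ρ = 0.3 and 0.6% at ρ = 0.5, well below 5%.

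**Approach effect at 12 months.** The regression on the 12-month value uses one observation per patient and is not affected. A model with approach-by-visit terms, read at 12 months, also has an essentially correct standard error if the variance is similar across visits.

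**The case against.** The strongest reply is that the section never says visits will be treated as independent. The sentence opens by recognising that the outcomes are repeated and sets them apart from the ordinary regressions before it. In SPSS the generalized linear model family can be run with a repeated subject, which makes it GEE. The wording may be shorthand for that, with the details in a fuller plan that is not shown. This stands as far as it goes: the inflation is a consequence of fitting the model as named, not a stated property of the plan. It does not remove the point, because the article names a method, and the method as named does not fit the data assigned to it.

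Second, the analysis is additional, as the word *also* shows, and the study was sized for a comparison at 12 months that visit correlation does not touch. This stands too. A reader might infer that the type I error of the trial's primary result is tripled or quadrupled. The documents do not support that. They do not say that a visit-averaged effect will be tested, let alone that it decides the primary outcome, and a factor of three to four holds only for ρ of about 0.43 to 0.67. What remains is that no time point is attached to the primary outcome in its own section, so a visit-averaged HHS result could be reported prominently.

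Third, the calculation assumes complete visits, while the plan states: "Anticipating failure to follow up of 40%, inclusion of at least 69 patients per intervention group, or 138 in total, is required". Fewer visits per patient mean less inflation. With two visits and ρ = 0.5, D = 1.5 and the true error is 2 × [1 − Φ(1.96/√1.5)], about 11%. The size falls, the direction does not change.

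One might also suppose that the similarly named general linear model for repeated measures was meant, which would drop patients with any missed visit. That is a guess about intent, and the point does not rest on it.

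**Conclusion.** The point holds in conditional form. The Statistical analysis section assigns repeated outcomes to a model class that, as named, assumes independence, and it specifies no within-patient correlation. Fitted that way, the HHS approach effect averaged over three visits would be tested at a true level of about 12% to 22% for ρ from 0.3 to 0.8, about 17% at 0.5. The pain score, with four occasions, would fare somewhat worse. Approach-by-visit tests would be conservative. These sizes rest on an assumed, equal correlation and complete visits.

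The 12-month regression, the sample size and the propensity adjustment are not called into question. This is a wording correction worth making before analysis. It is not evidence that the primary comparison is invalid.

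**What to change.** Replace the sentence on Generalized Linear Models with one that states:
- for the HHS and other continuous repeated outcomes, a linear mixed model for repeated measures; for non-continuous repeated outcomes, GEE with robust standard errors;
- the patient as the cluster;
- fixed effects for approach, visit, approach-by-visit and the propensity score;
- the approach contrast read at 12 months, the time point used in the Sample size section.

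The cost is one sentence and slightly more analysis work, in the same software and with the same data. Confidence intervals for any visit-averaged effect will be wider than under independence, as they should be. Whether to allow for clustering by surgeon is a separate matter and is not part of this change.
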